## **SUMMARY of PROTOCOL**

|                                     |                                                                                                                                                                                                                                                                                                                                                                                                                                                                                                                                                                                                                                                                                                             |
|-------------------------------------|-------------------------------------------------------------------------------------------------------------------------------------------------------------------------------------------------------------------------------------------------------------------------------------------------------------------------------------------------------------------------------------------------------------------------------------------------------------------------------------------------------------------------------------------------------------------------------------------------------------------------------------------------------------------------------------------------------------|
| 1. Title                            | The association between geographical area and mosquito-borne diseases exposure risk in Bangkok                                                                                                                                                                                                                                                                                                                                                                                                                                                                                                                                                                                                              |
| 2. Acronym                          | GeoMosquito                                                                                                                                                                                                                                                                                                                                                                                                                                                                                                                                                                                                                                                                                                 |
| 3. Type of study                    | 
A cross-sectional school-based seroprevalence study among children aged 10-15 years. Sero-conversion to dengue virus and chikungunya virus exposure will be measured by the Dengue IgG Rapid Diagnostic kit and the Chikungunya IgG Rapid Diagnostic kit, respectively.
 
A cross-sectional questionnaire study. Questionnaire about KAP about mosquito-borne diseases among their parents who enrolled in the seroprevalence study
 
A prospective observational study of mosquito sampling study in schools and in the homes of 10% of the recruited children using sticky traps
                                                                                                         |
| 4. Rationale                        | Specific places have the potential for being hotspots of viral transmission because of their conduciveness for mosquitoes and their environmental and demographic characteristics that enable these mosquitoes to find and bite their hosts. These areas are predicted to be responsible for the multiplication of cases at a hyperlocal level. Places that are hyper-connected (by transport networks) contribute significantly to viral spread at a city-wide scale, not least from the above-mentioned hotspots. We hypothesize that hyper-connected intra-urban districts will have a higher exposure to dengue and chikungunya, dependent upon the predicted environmental suitability for mosquitoes. |
| 5. Principle objective              | Assess the extent of dengue virus and chikungunya virus seropositivity, using Rapid Diagnostic tests for IgG in ~1000 school children, aged 10-15 years of age, spread across 2-3 schools of four different environments classified by their degree of connectivity and extent of built-up area, is associated with highly connected areas and predicted high mosquito abundance areas within Bangkok.                                                                                                                                                                                                                                                                                                      |
| 6. Secondary objectives             | 
Collect mosquito samples in these 8-12 schools
 
Assess knowledge, attitude, and practice about mosquito-borne disease, control measures, and vaccine acceptance among parents
                                                                                                                                                                                                                                                                                                                                                                                                                                                                                                                  |
| 7. Principle criteria of evaluation | Seroprevalence rates                                                                                                                                                                                                                                                                                                                                                                                                                                                                                                                                                                                                                                                                                        |
| 8. Secondary criteria               | 
Mosquito numbers
 
Answers to a questionnaire about knowledge, attitude, and practice
                                                                                                                                                                                                                                                                                                                                                                                                                                                                                                                                                                                                           |

|                                         |                                                                                                                                                                                                                                                                                                                                                                                                                                       |
|-----------------------------------------|---------------------------------------------------------------------------------------------------------------------------------------------------------------------------------------------------------------------------------------------------------------------------------------------------------------------------------------------------------------------------------------------------------------------------------------|
|                                         | about mosquito-borne disease, control measures, and vaccine acceptance among parents                                                                                                                                                                                                                                                                                                                                                  |
| 9. Subjects and numbers of subjects     | 
~ 1000 children 10-15 years of age for DENV and CHIKV seroprevalence study
 
~ 1000 parents of children from the seroprevalence study for a questionnaire study
 
~ 100 homes for mosquito sampling study
                                                                                                                                                                                                            |
| 10. Inclusion criteria                  | - Acceptance to participate                                                                                                                                                                                                                                                                                                                                                                                                           |
| 11. Exclusion criteria                  | - Refusal to participate or suffering from any concurrent infection or with any physical or mental disability.                                                                                                                                                                                                                                                                                                                        |
| 12. Material/ Biological samples        | 
- Finger-prick blood sample for use with Rapid Diagnostic Kit
 
- Adult mosquitoes
                                                                                                                                                                                                                                                                                                                                        |
| 13. Individual data collection and flow | 
For each participating child:
 
 
- information on age, sex and history of infection
 
- place of residence (longitude & latitude)
 
 
KAP questionnaire for parents/care givers – age, sex, address, education level
                                                                                                                                              |
| 14. Study timeline                      | 
Estimated start date of enrollment: 01/06/2024
 
Enrollment period: 6 months
 
Duration of subject's participation:
 
 
- 4 months for mosquito sampling study
 
- 1 day for seroprevalence study and questionnaire
 
 
Total estimated study duration: 1 year
 
Data analysis: 6 months
 
Data storage period: 2 years after the last publication
 |
| 15. Number of centres                   | 8-12 schools                                                                                                                                                                                                                                                                                                                                                                                                                          |
| 16. Expected results                    | Sero-prevalence rates for dengue and chikungunya stratified by age, sex and environmental typology (4 types: High vs. Low centrality and High vs Low vegetation) of home and school. Mosquito abundance according to environmental typology. KAP on dengue and chikungunya.                                                                                                                                                           |

# 1. SCIENTIFIC JUSTIFICATION OF THE RESEARCH

## Background

Mosquito-borne diseases are those spread by the bite of an infected mosquito. *Aedes* spp. can transmit dengue virus (DENV), chikungunya virus (CHIKV), zika virus and yellow fever virus. In Thailand, dengue and chikungunya pose a significant public health concern, particularly among adolescents. Dengue fever is a disease that has no specific antiviral treatment but is managed supportively. Currently, the care and treatment of dengue fever patients has become much more effective. However, it is still observed that the mortality rate is approximately 0.1 to 0.5 percent, resulting in significant losses. Chikungunya is a viral illness characterized by sudden onset of high fever, joint pain, rash and myalgia. It can cause persistent joint pain that may last for months or years among adults but mild joint pain in children. However, neurological complication is reported frequently among children. There is also no specific antiviral treatment for chikungunya, so management focuses on supportive care to alleviate symptoms.

Prevention of dengue and chikungunya infection involves measures to reduce mosquito breeding/oviposition sites, and personal protective measures, including the use of mosquito repellents and wearing long-sleeved clothing, are also recommended. Currently, dengue vaccines are available and can prevent infection and decrease severity, but remain controversial because of potential increased severity upon infection with DENV in naïve individuals – the phenomenon known as Antibody-dependent enhancement. There is no available chikungunya vaccine.

Dengue and chikungunya are associated with a wide range of socio-economic factors that alter the risk of exposure to infectious mosquitoes and which can vary at very local scales [1-8]. However, these associated risk factors are not systematic [9,10], likely influenced by the role of human mobility in ferrying the virus from places of high environmental risk throughout the city [11-13]. Indeed, low risk mosquito abundance areas do not necessarily lead to reduced exposure to virus and the key factor seems to be the extent of connectedness of an area. Analyses conducted in Bangkok have identified specific socio-economic factors associated with dengue cases, but whose association with dengue incidence radically alters and improves when factoring in the Bangkok transport matrix (connectivity among the 180 Khwaeng) and differs from when just using physical distance (Table 1). However, clinical dengue cases make up only a fraction of the true number of DENV infections and may be subject to reporting bias. A more robust measure of exposure is therefore using serology surveys across a wide range of age groups.

**Table 1.** Effect of matrices of distance and transport connectivity among subdistricts on association of SE variables with dengue cases in Bangkok. Shown are parameter estimates and percentage of variation explained in the multivariate statistical analyses.

|                  | Transport matrix |        | Distance matrix |        |
|------------------|------------------|--------|-----------------|--------|
|                  | w/o              | with   | w/o             | with   |
| No education     | 0.047            | 0.081  | 0.047           | 0.072  |
|                  | 2.2%             | 36.9%  | 2.1%            | 73.1%  |
| % Cement houses  | 0.0035           | 0.0045 | 0.0034          | -0.027 |
|                  | 11.5%            | 36.9%  | 10.8%           | 0.03%  |
| N° houses (100s) | 0.0023           | 0.0023 | 0.002           | 0.0036 |
|                  | 46.6%            | 18.9%  | 48.1%           | 23.3%  |

As a pilot study, prior to roll-out across Bangkok, dengue virus sero-prevalence rates were measured using the Panbio Indirect IgG ELISA on stored blood samples from 272 children aged 3-15 years from within Bangkok. These were mapped according to their homes and schools, whose environmental typology (satellite imagery for vegetation index, height and surface of buildings) and degree of centrality (services density, frequency of transportation and visits using social media data) were established (see Figures below). The association of the degree of centrality (high vs. low) and the type of environment (Open vs. densely built-up) with sero-prevalence rates was then analysed by logistic regression, taking into account the ages of the individuals.

From this retrospective study, the median (IQR) age of the samples was 10.7 (7.6-12.6) years. DENV sero-prevalence rates among children 3-9 years and 10-15 years were 6.5% and 37.2% respectively. Children going to schools characterized by an open environment or one of low centrality had much lower sero-prevalence rates (Open vs. dense: 16.8% vs. 27.1%; Low vs high centrality: 14.8% vs. 25.2%). There was no difference in sero-prevalence rates according to the degree of centrality of their homes. However, sero-prevalence rates in homes in open environments were higher (27.1% vs. 12.6%) (Fig. 3).

**Figure 3.** Sero-prevalence rates according to landscape category and centrality in children's homes and schools

[figure not shown]

Suwanbamrung et al. [14] conducted a cross-sectional study among children aged 8-13 years from 50 public schools in Kanchanadit district to assess the correlation between knowledge, attitude and practice (KAP) in dengue infection including prevention method compare between children with and without dengue infection experience using 32-items questionnaire. The study shows no significant difference in KAP mean score between the 2 groups, but the children with previous dengue infection had better preventive practice than the other group (OR 1.34, 95%CI 1.03-1.75,  $P=0.032$ ). The study also notes that most children (more than 70%) reported that their source of dengue information came from their teacher. Thus, in addition to the sero-prevalence study, we are also interested in assessing levels of KAP concerning dengue and provide more information about dengue infection and prevention, which can then be applied in their school and household.

Vongpunsawad et al. [15] conducted sero-prevalence surveys of CHIKV and DENV in Thailand, in which 835 serum samples were obtained from individuals living in central and southern Thailand by using anti-CHIKV and anti-DENV IgG antibodies commercial enzyme-linked immunosorbent assays. Overall seropositivity of CHIKV in children aged < 15 years was 10.3%, of which 17.8% among participants from the south and 2.6% among participants from central Thailand. Seropositivity of DENV was 31.9% among children aged < 9 years in both in the southern and central parts, 55.4% among children aged 10-19 years among southern participants and 62.5% among children aged 10-19 among central participants. The current situation in Bangkok is unknown, but a large scale outbreak occurred all of Thailand in 2018-2019 and *Aedes aegypti* was incriminated as the major vector [16]. We thus anticipate that the sero-prevalence rates will be influenced by the environmental typology as for DENV.

Based on these preliminary findings, this current project aims to expand this sero-prevalence study in a prospective school-based study in children aged 10-15 years old for both DENV and CHIKV infections.

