## 2. **OBJECTIVES**

### **Primary objective:**

To address the extent to which (satellite-) predicted and empirically validated mosquito abundance and mapped transport/mobility connectedness among Khwaeng do associate with DENV and CHIKV exposure as measured by sero-positivity. Coupled with a detailed geographic information system (GIS) of Bangkok, including fine scale meteorological data, will subsequently enable fine scale agent-based simulation models to test *in silico* the efficacy of implementing vector control in a variety of locations.

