## 3. **METHODOLOGY**

### **3.1. Type of research**

This study divides into 3 parts

1. A cross-sectional school-based sero-prevalence study among children aged 10-15 years. Sero-conversion to dengue virus and chikungunya exposure will be measured by Dengue IgG Rapid Diagnostic kit and Chikungunya IgM/IgG Rapid Diagnostic kit, respectively (SD Bioline).
2. A cross-sectional questionnaire study. The questionnaire about KAP about mosquito-borne diseases among their parents who enrolled in sero-prevalence study
3. A prospective observational study of mosquito sampling study in schools and in the homes of 10% of the recruited children using sticky traps

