### **3.2. Evaluation criteria**

#### **Principle evaluation criteria:**

Epidemiological read-out – sero-prevalence

To assess the association of centrality with exposure to DENV and CHIKV, we will perform a sero-prevalence study using Rapid Diagnostic kits on children 10-15 years spread across 8-12 schools in Bangkok.

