## 9. STATISTICAL CONSIDERATIONS

Sample size:

Based on the preliminary data showing a difference in prevalence rates according to school centrality and environmental typology (approximately 26% vs 15%), we estimate a necessary sample size of ~210 children for each of the four typologies (Central+/Environmental+, Central+/Environmental-, Central-/Environmental+, Central-/Environmental-).

Sample size was calculated as follows [17]

$$n = (Z_{\alpha/2} + Z_{\beta})^2 \cdot [p_0(1 - p_0) + p_1(1 - p_1)] (p_0 - p_1)^2$$

Where n is the required sample size per treatment arm,  $Z_{\alpha}$  and  $Z_{\beta}$  are constants set by convention according to the accepted  $\alpha$  error and whether a one-sided or two-sided effect,  $p_0$  is the proportion sero-positive in area type 0 (ie Central + or Environment +), and  $p_1$  the proportion areas type 2 (Central – or Environment –).

Assuming a  $p < 0.05$  as acceptable and a study with 90% power, the following constant values are:  $Z_{\alpha/2} = 1.96$  and  $Z_{\beta} = 0.84$ .

Because our preliminary data indicated variation within school centrality and environmental typology, (coefficient of variation ranging from 0.6-1), we used the following formula to estimate the number of different sites for each typology.

$$\text{Site number per typology} = 1 + (Z_{\alpha/2} + Z_{\beta})^2 \cdot [p_0(1 - p_0)/n + p_1(1 - p_1)/n + k^2(p_0^2 + p_1^2)] (p_0 - p_1)^2$$

Where k is the coefficient of variation and n the number of individuals as calculated above. Using  $n=210$  and  $k=0.6$  to 1, we would need at least two and optimally three schools per environmental typology with 80-100 children per school.

Sero-positivity (as defined by the manufacturers instructions) will be analysed by logistic regression with age, sex and centrality (high vs. low) and environmental typology (Open vs Dense) as explanatory variables using R. School mosquito densities will also be included as an explanatory variable. In the subset of individuals collecting mosquitoes in the homes will be taken into account in a separate analysis. Mosquito densities will also be analysed with respect to the environmental typology and meteorological parameters.

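### Chikungunya association is part of the primary objective, but the only sample size and power statement rests on dengue rates, so power for chikungunya is not shown

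*Protocol*

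**What the plan says.** Section 2 asks how far predicted mosquito abundance and connectedness "do associate with DENV and CHIKV exposure as measured by sero-positivity". It does not rank the two viruses. Section 3.2 repeats the pairing as the principal criterion: "To assess the association of centrality with exposure to DENV and CHIKV, we will perform a sero-prevalence study".

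Section 9 has the only sample size calculation. From preliminary rates of about 26% and 15% it derives "a necessary sample size of ~210 children for each of the four typologies", and it words the power as 90% while setting the power constant to 0.84. The preliminary rates come from the pilot in the Background, where "dengue virus sero-prevalence rates were measured using the Panbio Indirect IgG ELISA on stored blood samples from 272 children aged 3-15 years". The school contrasts, in per cent, were "Open vs. dense: 16.8% vs. 27.1%; Low vs high centrality: 14.8% vs. 25.2". That pilot reports no CHIKV result.

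The CHIKV rates in the Background come from an earlier survey of children under 15: 10.3% overall, and "17.8% among participants from the south and 2.6% among participants from central Thailand". The same paragraph says that the present level in Bangkok is not known, mentions the 2018-2019 outbreak, and expects typology to act on CHIKV as it does on DENV.

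Section 9 then plans a single logistic regression of sero-positivity on age, sex, centrality, environment and school mosquito density. Positivity follows the manufacturer's instructions. Section 3.1 names a "Chikungunya IgM/IgG Rapid Diagnostic kit"; item 3 of the summary table names an IgG kit.

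**The concern.** A power statement should cover the primary objective it stands beside. Here one of the two viruses in that objective has no assumed prevalence, no target effect and no precision. Because the required number depends strongly on prevalence, a figure derived near 20% cannot be carried to an outcome that may be a few per cent.

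If CHIKV prevalence is still low, the planned five-variable model would be fitted to few positives, and a null CHIKV result could be reported without the warning that the study was never sized to find an association. Section 5.3 offers the findings on place and exposure to both viruses as the study's main benefit, so the strength of the CHIKV claim matters.

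**Working it through.** **1. The protocol's own figure.** Section 9's formula, read as a ratio, with p0 = 0.26, p1 = 0.15 and constants 1.96 and 0.84:

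n = (1.96 + 0.84)² × [0.26 × 0.74 + 0.15 × 0.85] / 0.11² = 7.84 × 0.3199 / 0.0121 = 207.

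This reproduces the ~210. The constant 0.84 is the value for 80% power. For 90% it is 1.2816, and n = (3.2416)² × 0.3199 / 0.0121 = 278. So ~210 per group delivers 80% for dengue, before any between-school variation.

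**2. Expected CHIKV positives.** 1000 × 0.026 = 26, or 6.5 per typology and 26 / 5 = 5.2 per explanatory variable. At 5% (an assumed intermediate value) there would be 50, and at 10.3% there would be 103.

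**3. Effect assumed for CHIKV.** The protocol gives none in numbers. Taking its expectation that CHIKV behaves like DENV, two readings are possible:
- risk ratio 26/15 = 1.73
- odds ratio (0.26/0.74)/(0.15/0.85) = 1.99, which is the scale of the planned logistic model.

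**4. Power for a main effect.** With 1000 children spread evenly over four typologies, each level of centrality or environment has 500. Power = Φ( (p0 − p1) / √{[p0(1 − p0) + p1(1 − p1)]/500} − 1.96 ), with the two rates centred on the overall prevalence.

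At 2.6%:
- Risk ratio 1.73: p1 = 2 × 0.026 / 2.733 = 0.0190 and p0 = 0.0330. Difference 0.01395, standard error √(0.05055/500) = 0.01005, so Φ(1.39 − 1.96) = 28%.
- Odds ratio 1.99: p0 = 0.0344 and p1 = 0.0176. Difference 0.01683, standard error √(0.05051/500) = 0.01005, so Φ(1.67 − 1.96) = 39%.

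| CHIKV prevalence | Positives in 1000 | Power, risk ratio 1.73 | Power, odds ratio 1.99 |
|---|---|---|---|
| 2.6% | 26 | 28% | 39% |
| 5% | 50 | 50% | 63% |
| 10.3% | 103 | 82% | 90% |

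At 2.6%, 80% power would need about 2,040 per level (risk ratio) or 1,400 (odds ratio). With 500 per level, 80% power is reached at a prevalence of about 9.8% (risk ratio) or 7.6% (odds ratio).

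**5. School clustering.** All of these treat children as independent. Section 9 cites a between-school coefficient of variation of 0.6 to 1, from the dengue pilot. Putting 0.6 into its site formula, with 4 to 6 schools per level and risk ratio 1.73, gives about 12-15% power at 2.6% and 16-23% at 10.3%. Using that coefficient for CHIKV is an assumption, so these figures show direction rather than a forecast.

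**6. Test error.** The protocol gives no kit specificity. With an assumed 97%, 98% or 99%, and 2.6% truly positive with full sensitivity, false positives per 1000 are 974 × 0.03 = 29, 974 × 0.02 = 19 and 974 × 0.01 = 10, against 26 true positives.

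**The case against.** The strongest reply is that 2.6% is not a planning value. It is an earlier survey's figure for central Thailand and all children under 15, whereas this study enrols ages 10-15 in Bangkok after a national outbreak, and the protocol says the level is unknown. That stands. A reader might infer that the study will have too few CHIKV positives; the documents support this only if prevalence has stayed near 2.6%. At 10.3% power would be 82-90% before clustering. An unknown prevalence does not, however, supply the missing assumption: the power statement still says nothing about CHIKV.

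A reader might also infer that the raw CHIKV seroprevalence would be mostly false positives. With the assumed specificities, false positives outnumber true ones only near 97%, and only at 2.6%; at 99% they are 10 of 36. The documents give no specificity, so this justifies a sensitivity analysis and no more.

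Nor do the sections define two different CHIKV endpoints. The summary table (items 3 and 5), section 5 and section 5.1 A all describe an IgG measurement, and a two-band kit is compatible with that. What remains is that no sentence says how an IgM-only result is scored.

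Finally, the summary table gives seroprevalence rates as the principal criterion, and estimation is feasible: 26 in 1000 has an exact 95% interval of about 1.7% to 3.8% before clustering. That supports keeping CHIKV as an estimate. It does not supply power for the association in section 2.

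**Conclusion.** The point holds as a mismatch between objective and justification: the association objective covers both viruses, and the sample size and power are derived for dengue alone. How much this matters depends on a prevalence that the protocol does not know: 28-39% power at 2.6%, 50-63% at 5%, 82-90% at 10.3%. These figures assume a CHIKV effect as large as the dengue pilot's, equal numbers per level and no clustering; clustering lowers them all. That the CHIKV analysis must fail, or that a null result would necessarily be misread, is not established. The 90% attached to the dengue calculation is also wrong on the protocol's own constant, so it should not be carried into any revised statement. This should be corrected, and it can be done without more children or schools.

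**What to change.** - In section 9, state that the sample size and power apply to the DENV association only. Give the power as 80% for about 210 per group, before between-school variation; 90% would need about 278.
- Keep CHIKV seroprevalence as an estimate, with an interval that accounts for clustering by school.
- Label the CHIKV-typology and CHIKV-mosquito associations exploratory, and say that a null result is not evidence of no association. If few positives are seen, use a penalised logistic model that keeps the exposures of interest. Mosquito density must stay in, because mosquito abundance is named in the primary objective.
- State once that a positive CHIKV result means the IgG band, since section 3.1 names a two-marker kit and section 9 defers to the manufacturer.
- As a sensitivity analysis, report CHIKV prevalence over a stated range of kit specificity.

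The cost is protocol wording and a small amount of analysis. The downside is a more modest CHIKV claim.
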